## **Randomisation**

Participants will be randomized 1:1 to the PCI performed using standard care or technology-assisted PCI in blocks to ensure balanced distribution of the treatment groups at all times. The study team will enter the participant screening information into the electronic data capture (EDC) system after informed consent has been obtained. Once the participant is determined to be eligible prior to the Index Procedure the study team will randomise the participant using the EDC. The Investigator will be advised of this and the allocated method of PCI will be performed. The participant will ideally remain blinded to the method of PCI performed.

## **Concomitant Therapy**

Medications to be reported in the Case Report Form (CRF) are concomitant prescription medications, over-the-counter medications and supplements.

# Study Intervention Discontinuation and Participant Discontinuation/ Withdrawal

In the event that the participant is randomized but does not go ahead to have PCI or there is a requirement to move from technology-assisted PCI to manual PCI they will not be discontinued from the study and the remaining study procedures should be completed as indicated by the study protocol. Any discontinuation of the participant after the PCI is described in Section 6.1.

## **Participant Withdrawal**

Once the participant has been enrolled in the study, s/he may withdraw consent to participate in the study at any time without prejudice. Participation in this clinical investigation is entirely voluntary. Likewise, there may be a reason identified by the Investigator that deems the participant no longer suitable for the study. If participant safety is not at risk, all reasonable efforts should be made to retain a participant prior to consideration for withdrawal as this can significantly impact data quality. In either case, the Investigator will contact the appropriate authority to discuss the circumstances for discontinuation/withdrawal. Discontinuation or withdrawal may occur for any of the reasons listed below (this list is not all inclusive).

- Participant is uncooperative with compliance of required study tests, medical management and/or procedures
- Investigator determines that participant has developed a condition in which continued participation in the study is considered potentially harmful to the participant
- Participant withdraws their consent
- Participant is lost to follow-up
- Participant has a significant protocol violation
- Participant incorrectly enrolled in the study
- the appropriate authority terminates the study

## **Lost to follow up**

A participant will be considered lost to follow-up if he or she fails to return for scheduled visits and is unable to be contacted by the study site staff.

The following actions must be taken if a participant fails to return to the clinic for a required study visit:

- The site will review the Electronic Medical Records (EMR) and/or contact the referring Cardiologist to determine if the participant is alive.
- The site will attempt to contact the participant and reschedule the missed visit ( within 1 month) and counsel the participant on the importance of maintaining the assigned visit schedule and ascertain if the participant wishes to and/or should continue in the study.
- Before a participant is deemed lost to follow-up, the investigator or designee will make every effort to regain contact with the participant (where possible, 3 telephone calls and, if necessary, a certified letter to the participant’s last known mailing address or local equivalent methods). These contact attempts should be documented in the participant’s medical record or study file.
- Should the participant continue to be unreachable, he or she will be considered to have withdrawn from the study with a primary reason of lost to follow-up.

# Study Assessment and Procedures

## **Screening Assessment**

The following evaluations are to be performed up to 30 days prior to the PCI

- Obtain informed consent using the study-specific Informed Consent Form
- Inclusion/Exclusion screening
- Document medical history and demographics
- Complete physical exam
- Complete vital signs (heart rate, blood pressure) and measure height and weight
- Medication assessment
- 12 lead electrocardiogram
  - Blood assays for full blood count, renal function, cardiac enzymes, creatine kinease (CK) & creatine kinease myocardial band (CK-MB) and/or Troponin (within 7 days of index procedure)

## **Index Procedure (PCI)**

Participants who meet the eligibility criteria will be randomized within 24 hours prior to their PCI.

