## **Other Measures/ Procedural Characteristics**

The objective of this study is to compare standard PCI with technology-assisted PCI to collect real-world data. When the PCI is being performed in conjunction with a diagnostic procedure, all efforts should be made to isolate the PCI procedural characteristics from the diagnostic procedure. At the end of the diagnostic procedure or alternatively to coincide with the PCI procedure time record the contrast, fluoroscopy time, DAP & AK at the end of the diagnostic procedure. When the PCI procedure is finished, record the values for these characteristics accumulated during the PCI procedure and not the diagnostic procedure. Procedures will be identified as staged (PCI only) or ad-hoc (LHC possible PCI). Any requirement to move from technology-assisted PCI to standard care will also be captured.

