# Study Design

## **Overview**

This is a randomized controlled trial of the CorPath GRX System versus standard PCI to compare participant outcomes at 72 hours post-procedure or hospital discharge, day 30 and 1 year.

The study population will consist of all consecutive participants undergoing PCI at Liverpool Hospital being asked to provide written informed consent prior to PCI and meet the eligibility criteria.

The study will randomize 300 participants equally into the 2 arms:

- Arm 1: PCI using the CorPath GRX System
- Arm 2: PCI using standard care

All enrolled participants will be followed post procedure through hospital discharge or 72 hours, whichever occurs first. The follow up will occur at day 30 and 1 year post-procedure

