## **Exclusion Criteria**

- The investigator determines that the participant or the coronary anatomy is not suitable for robotic-assisted PCI.

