## **Strategy for Recruitment and Retention**

All participants who are presenting to Liverpool Hospital for angiography and potential PCI will be asked to participate in this study. Participants will be consented according to Section 11.2 of the protocol.

After the participant has provided consent, the Investigator will confirm eligibility against the inclusion and exclusion criteria. If the participant meets the criteria they will be randomized according to Section 5.3 of the protocol. The participant and their significant others will be blinded to the method of PCI.

Participants will be asked to return for study visits as identified in Section 7. The participant will be contacted prior to the visit to confirm the appointment. If they are unable to attend all efforts will be made to collect the measurements as per the protocol.

If participants withdraws from the study please refer to Section 6.

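### In ad-hoc cases the protocol lets an open allocation come before the diagnostic angiogram that settles PCI indication and robotic suitability

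*Protocol*

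**What the plan says.** - **Timing.** Section 7.2 (Index Procedure): "Participants who meet the eligibility criteria will be randomized within 24 hours prior to their PCI". Section 5.3 (Randomisation): "Once the participant is determined to be eligible prior to the Index Procedure the study team will randomise the participant using the EDC". The investigator is then told the arm, and section 8.1 calls the trial open-label.
- **Who is approached.** The section Strategy for Recruitment and Retention states: "All participants who are presenting to Liverpool Hospital for angiography and potential PCI will be asked to participate in this study". Section 3.1 (Overview) describes a different group: "The study population will consist of all consecutive participants undergoing PCI at Liverpool Hospital".
- **Ad-hoc cases are in.** Section 2.6: "Procedures will be identified as staged (PCI only) or ad-hoc (LHC possible PCI"). The same section limits contrast, fluoroscopy and dose values to the PCI phase and leaves out the diagnostic phase.
- **Eligibility.** Section 4.1 requires a clinical indication for PCI. The only exclusion, in section 4.2, is: "The investigator determines that the participant or the coronary anatomy is not suitable for robotic-assisted PCI". The Schedule of Events (3.3) ticks inclusion and exclusion under Screening only, and section 7.1 lets screening take place up to 30 days before PCI.
- **After allocation.** Section 6.0 provides for this case: "In the event that the participant is randomized but does not go ahead to have PCI". Such participants stay in the study, as do those moved from robotic to manual PCI. Section 6.1, however, lists "Participant incorrectly enrolled in the study" among the reasons for discontinuation or withdrawal.
- **Before allocation.** Section 4.3 treats people who consent but are not then randomised as screen failures.

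**The concern.** In an ad-hoc case with no earlier coronary imaging, neither the need for PCI nor the fit of the anatomy to the robot can be confirmed until the diagnostic angiogram. If the participant has been randomised by then, two things can follow.

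First, some randomised participants will turn out not to need PCI. They have no PCI-phase dose, PCI time, PCI contrast volume, residual stenosis or technical success result.

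Second, suitability for the robot becomes a judgement made by someone who knows the arm. In the standard arm it changes little, because manual PCI goes ahead either way. In the robotic arm it decides whether the allocated treatment is delivered. If it also decides who is counted, the arms are no longer compared as randomised. An analysis plan can define analysis sets, but it cannot move the point of randomisation.

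**Working it through.** **1. Sequence of events**

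| Step | Staged, anatomy known | Ad hoc, no earlier imaging |
|---|---|---|
| Indication and anatomy known at screening | Yes | No |
| Randomisation before the index procedure (5.3, 7.2) | After eligibility is known | Can be before eligibility can be known |
| Angiogram | Confirms what is known | First evidence on both criteria |
| Suitability judged with arm known | Little scope | Possible |

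The text also allows a safe order in ad-hoc cases. Section 7.2 counts back from the PCI, not from the angiogram, so randomising between the two would comply. The protocol does not say which order applies, and no section asks for eligibility to be rechecked after the angiogram.

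**2. Effect on the stated power**

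Inputs from section 8.1: 150 per arm; control mean 1284 mGy, SD 180; intervention SD 142.83; 20% reduction; two-sided 5%; stated power above 99%.

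- Difference: 0.20 × 1284 = 256.8 mGy, so the intervention mean is 1027.2.
- Pooled SD: √((180² + 142.83²)/2) = 162.48.
- SE: 162.48 × √(2/150) = 18.76. Then z = 256.8/18.76 = 13.69, and power = Φ(13.69 − 1.96), about 1.000. The stated figure is reproduced.
- On these SDs, 15 per arm already gives 99% power.

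The protocol gives no rate of randomised participants without PCI. Let *f* be that fraction. It is an assumption, shown over a range and taken as equal in both arms.

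(a) *No PCI, no value:* n per arm = 150(1 − f), difference unchanged.

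(b) *No PCI, scored as zero dose:* difference = 256.8(1 − f); variance in each arm = (1 − f)·SD² + f(1 − f)·mean²; n = 150 per arm.

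| f | n per arm in (a) | Power in (a) | Difference in (b), mGy | Power in (b) |
|---|---|---|---|---|
| 10% | 135 | >0.999 | 231.1 | 0.999 |
| 20% | 120 | >0.999 | 205.4 | 0.955 |
| 30% | 105 | >0.999 | 179.8 | 0.808 |
| 40% | 90 | >0.999 | 154.1 | 0.628 |
| 50% | 75 | >0.999 | 128.4 | 0.467 |

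Worked line for (b) at 30%:
- Control variance: 0.7 × 180² + 0.21 × 1284² = 368,898.
- Intervention variance: 0.7 × 142.83² + 0.21 × 1027.2² = 235,860.
- SE: √((368,898 + 235,860)/150) = 63.5.
- z = 179.76/63.5 = 2.83, and power = Φ(0.87) = 0.808.

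Under (a), even f = 90% (15 per arm) leaves power at 0.991.

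**The case against.** The strongest reply is that the protocol states the right order: eligibility is confirmed first and randomisation follows, in the recruitment section, 5.3 and 7.2 alike. The recruitment sentence says who is asked, not who is randomised. A person whose angiogram rules out PCI could be a screen failure under 4.3. The Schedule of Events places randomisation under the index procedure, not under screening. Section 6.0 keeps participants without PCI and those converted to manual PCI, and the incorrectly-enrolled item in 6.1 is one entry in a general list that nothing links to anatomy.

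Much of this stands, and it rules out some stronger readings that a reader might infer:
- *That the protocol randomises before eligibility as a rule.* It does not. It allows this in ad-hoc cases and is silent on the order.
- *That many participants are lost.* No ad-hoc share or no-PCI rate is given.
- *That those without PCI contribute nothing.* They lack procedural outcomes only. Section 6.0 keeps them in follow-up, so MACE and resource use are still collected.
- *That power collapses.* This needs a high no-PCI rate and zero-dose scoring, and neither is in the document.

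The reply does not close the gap. A site that checks eligibility at screening and randomises the day before follows 5.3, 7.2 and the Schedule as written, yet allocates before the two criteria can be known in an ad-hoc case. Section 6.0 foresees randomised participants who never have PCI, so the screen-failure route does not catch everyone.

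**Conclusion.** The point holds as a conditional risk of bias confined to ad-hoc cases. The protocol does not tie randomisation to the diagnostic angiogram, although the PCI indication and anatomical suitability can depend on it. Where a site randomises first, an unstated number of participants may have no procedural outcome, and suitability for the robot may be judged with the arm known, which matters in practice mainly in the robotic arm. Sections 6.0 (retain) and 6.1 (may withdraw as wrongly enrolled) leave open whether such a participant can be removed.

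The size of any bias cannot be computed, because the protocol gives neither the ad-hoc share nor the no-PCI rate. The stated power is not threatened if these participants simply have no value. It drops below 80% only under zero-dose scoring with a little over 30% affected. Both power results rest on the protocol's own means and SDs. The point is worth correcting as a cheap improvement; it does not show the design to be unsound.

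**What to change.** Amend the protocol as follows.

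- **5.3 and 7.2:** ad-hoc participants consent beforehand, as now, but are randomised in the EDC only after the diagnostic angiogram, once the operator has recorded that PCI will proceed and that the anatomy is suitable for robotic PCI. Staged cases with known anatomy may still be randomised within the 24 hours before PCI.
- **4.3:** those who fail this check are screen failures.
- **6.1:** state that the incorrectly-enrolled reason does not remove anyone from the analysis after allocation, and reconcile it with 6.0.
- **Consistency:** bring 2.6, 3.1, the Schedule of Events (3.3), the recruitment section, 5.3, 6.0, 6.1 and 7.2 into line on who is recruited, when eligibility is confirmed and when randomisation takes place.

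The cost is one amendment and a few minutes in the catheter laboratory per ad-hoc case for the EDC entry and robot set-up. No extra participants or procedures are needed.

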### Peri-Procedure Study Medication Regimen

Follow standard institutional and/or stent manufacturer’s guidelines for recommended anticoagulation regimen.

### Data to be collected prior to initiating PCI

- Operator and assistant details
- Arterial access site and side
- Procedure start time (Sheath insertion)
- PCI Start Time (Guide Catheter Insertion)
- American Heart Association/American College of Cardiology lesion classification

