### Overall Procedure Time Measure

Defined as the time measured from the insertion of the hemostasis sheath until the removal of the guide catheter

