### PCI Procedure Time

Defined as the time measured from the insertion of the guide catheter until removal of the guide catheter.

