# Data Management, Statistical Analysis and Record Keeping

## **Statistical Methods**

This is a double-arm, open-label, randomized controlled trial of the CorPath GRX System designed to evaluate the safety and effectiveness of the clinical and technical performance of the CorPath GRX System in the delivery and manipulation of coronary guidewires and stent/balloon catheters, and remote manipulation of guide catheters for use in PCI in comparison to standard of care. The analysis of data collected as part of the RCT will include, but may not be limited to, the Objectives and Measures outlined in Section 3.0 of this protocol. Continuous variables will be summarized using the number of observations, mean, standard deviation, median, min and max values. Categorical variables will be summarized with the number and percent in each category out of the number observed. Two-sided 95% confidence intervals may be calculated and two-sided p-values < 0.05 will be considered statistically significant.

The outcome of patient radiation exposure will be analysed using variance (ANOVA). As each participant may have multiple lesions, the outcome of clinical success at day 3 will be analysed using a two level multilevel models. Logit link will be used with a binomial distribution and restricted maximum likelihood (REML) will be used for estimation. Predictor variables in the models will include treatment group.

Technical success will analysed with Fisher’s exact test, comparing the proportion of participants with technical success between the two groups. Logistic regression will be used to compare technical success accounting for lesion complexity. For all other secondary outcomes, continuous outcomes will be measured using independent t-test (or non-parametric alternative depending on distributional assumptions), and categorical outcomes analysed by Fisher’s exact test. For outcomes measured repeatedly over time, multilevel models with an appropriate link functions will be used for analysis.

All statistical analyses will be performed using SAS software (version 9.4) or other widely accepted statistical or graphical software.

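### Overall Procedure Time includes the diagnostic angiogram in ad-hoc cases only, and the planned test ignores the staged/ad-hoc label that the protocol already records

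*Protocol*

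**What the plan says.** Section 2.6 of the protocol lists several time outcomes. Two matter here.

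- **Overall Procedure Time** (2.6.1): "Defined as the time measured from the insertion of the hemostasis sheath until the removal of the guide catheter". Section 7.2.2 records the matching start as "Procedure start time (Sheath insertion").
- **PCI Procedure Time** (2.6.2): "Defined as the time measured from the insertion of the guide catheter until removal of the guide catheter". Its start is the next line of the same list in 7.2.2, "PCI Start Time (Guide Catheter Insertion").

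For a PCI done together with a diagnostic study, the opening of Section 2.6 asks that "all efforts should be made to isolate the PCI procedural characteristics from the diagnostic procedure". To that end staff are to "record the contrast, fluoroscopy time, DAP & AK at the end of the diagnostic procedure", or alternatively to take the readings at the PCI procedure time. The same paragraph adds a label: "Procedures will be identified as staged (PCI only) or ad-hoc (LHC possible PCI").

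Section 8.1 says that for secondary outcomes other than those it names, "continuous outcomes will be measured using independent t-test", or a non-parametric alternative if the distribution calls for it. No covariate is mentioned for the times. Section 5.3 describes 1:1 block randomisation and states no stratification by staged or ad-hoc status.

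**The concern.** In an ad-hoc case the sheath is placed for the diagnostic angiogram. Sheath-to-guide-out time is then diagnostic time, plus any pause for a decision, plus the PCI. In a staged case the same measure contains no diagnostic angiogram. Section 4 recruits people who come for angiography with possible PCI, so ad-hoc cases should be common.

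One outcome therefore pools two quantities. The duration of the diagnostic part has no evident link to whether the PCI is robotic or manual. In an unadjusted test it acts as noise, and the mean in each arm moves with that arm's ad-hoc share. A real time cost or saving of the robotic technique becomes harder to detect and harder to carry over to a laboratory with a different case mix.

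**Working it through.** **The plan's own power figure.** The only one in the protocol concerns patient radiation (8.1): a 20% fall from 1284 mGy, SDs 180 and 142.83, 150 per arm.

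- Difference: 0.20 × 1284 = 256.8 mGy.
- Standard error: √((180² + 142.83²)/150) = √(52,800/150) = 18.76.
- Ratio: 256.8/18.76 = 13.7, so power is effectively 100%, in line with the stated figure of more than 99%.

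It does not involve the procedure clock. No power is claimed for any time outcome.

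**Model for Overall Procedure Time.** Let SD₀ be the SD without the diagnostic part, p the ad-hoc share, and m and s the mean and SD of the diagnostic part. Assume the diagnostic part is independent of the rest, and that SD₀ and the arm difference are the same in staged and ad-hoc cases.

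- Unadjusted: Var = SD₀² + p·s² + p(1−p)·m².
- With the label as a factor, the last term goes: Var = SD₀² + p·s².

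**Inputs.** 150 per arm comes from 8.1. SD₀, p, m and s are assumptions, because the protocol gives none of them.

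**Central case:** SD₀ = 20 min, m = 20 min, s = 8 min, p = 0.5.

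- Unadjusted variance: 400 + 0.5×64 + 0.25×400 = 400 + 32 + 100 = 532; ratio 532/400 = 1.33.
- Effective size: 150/1.33 = 113 per arm.
- A difference with 80% power without the diagnostic part is (1.96 + 0.84) × 20 × √(2/150) = 6.5 min. Its standardised value falls from 2.80 to 2.80/√1.33 = 2.43, so power is Φ(2.43 − 1.96) ≈ 68%.
- With the label: 400 + 32 = 432; ratio 1.08; 2.80/√1.08 = 2.70; power Φ(2.70 − 1.96) ≈ 77%.

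**Range:** SD₀ 15–25 min, m 15–25 min, p 30–70%, s fixed at 8 min.

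| Case | Added variance | Ratio | Power, unadjusted | Power, with label |
|---|---|---|---|---|
| Mildest: SD₀ 25, m 15, p 0.3 | 19.2 + 47.25 = 66.45 on 625 | 1.11 | 76% | 79% |
| Central | 32 + 100 = 132 on 400 | 1.33 | 68% | 77% |
| Worst: SD₀ 15, m 25, p 0.5 | 32 + 156.25 = 188.25 on 225 | 1.84 | 54% | 75% |

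A second, milder set of assumptions (SD₀ 20–30, m 10–20, s 5–10, p 25–75%) gives 67–79% unadjusted and 73–80% with the label.

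**Bias.** Allocation is random, so the expected ad-hoc share is equal in the arms. The SD of a chance difference in share at p = 0.5 is √(2×0.25/150) = 5.8 percentage points. With m = 20 min that moves the arm difference by about 1.2 min (one SD), and its expectation is zero.

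**The case against.** A reader might infer more than the protocol supports, in four ways.

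*That 2.6.1 breaches a firm rule in 2.6.* It does not. The instruction is to make all efforts, and the quantities it names are contrast, fluoroscopy time, DAP and air kerma. Elapsed time is not among them. An overall clock beside a PCI clock is a coherent pair.

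*That the diagnostic time can never be removed, so the trial has no clean time comparison.* Guide insertion time is recorded for every case, and PCI Procedure Time starts there. Section 2.6 itself accepts the PCI procedure time as a point for the readings. What cannot be separated is the gap between the end of the diagnostic part and the guide. Nothing in the protocol shows that this gap differs by arm: Sections 1.2 and 7.2.5 have the guide placed by hand first, and the listed CorPath steps come afterwards.

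*That the arm comparison is biased.* Randomisation rules out an expected bias.

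*That the clock should be restarted at the end of the diagnostic part for ad-hoc cases.* Staged cases would still start at the sheath and so include access, which ad-hoc cases would leave out. That is a new mixture under one name.

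It is also fair to say that covariates for a secondary outcome are often left to an SAP, and that the loss rests on assumed inputs. Both are true and limit the weight of the point. Still, Section 8.1 does state a test for these outcomes, and that test leaves out a label the same protocol collects.

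**Conclusion.** The point holds in a limited form. Overall Procedure Time measures different things in staged and ad-hoc cases, and the stated analysis does not use the label that tells them apart. The consequence is lost precision and a mean that depends on case mix, for one secondary outcome. No trial conclusion resting on radiation, and no sample-size decision, is affected.

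The size is conditional on figures that the protocol does not supply. With the diagnostic SD fixed at 8 min, variance rises by about 11% to 84% over the ranges tried. The power figures also rest on the t-test and on an arm difference common to both kinds of case. The label does not recover everything, because the spread of diagnostic times among ad-hoc cases remains. This is a worthwhile small improvement, not a flaw that threatens the trial.

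**What to change.** In Section 8.1, state that Overall Procedure Time will be compared with staged/ad-hoc status as a factor in a linear model, or stratified by it if a non-parametric method is used, and that it will also be summarised separately by that status. In the same place, name PCI Procedure Time as the main time comparison for the isolated PCI.

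Leave the definition in 2.6.1 and the recorded times in 7.2.2 unchanged.

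The cost is one model term and one extra split in a table. No new data field, participant or procedure is needed, because the label is already collected. The change should be made before any comparison by arm is seen.
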